### Sample size and analyses

The analyses for this trial will be performed on an intention-to-treat basis including all participants with outcomes data available. The primary outcome - a total score on the Autism Treatment Evaluation Checklist (ATEC) [64] (range 0–180) at Time Points 1, 2 and 3 will be analysed using a repeated measures ANOVA or via a General Linear Model (GLM). Based on the study investigator’s (AW and DC) clinical judgment in managing children with ASD, a score of 72 (50th centile) and a difference of 1SD = 32 (30th-70th centile) on the ATEC can represent clinically important improvement in ASD symptoms. The aim of this intervention is to look for a small-to-moderate effect size of 0.2–0.5 with 80 % power and two-sided alpha of 0.05. This will require a sample of approximately 64 participants per treatment group. Allowing for a 10 % drop-out rate, 70 participants will be required per treatment group, thus, the trial aims to recruit a total of up to 140 participants.

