### Baseline assessments, primary and secondary measures

A combination of direct observation and play-based assessments administered by a research -accredited ADOS assessor will be conducted on children with ASD. This will include parent self-reports on a range of child-related and ASD specific symptoms and behaviours. In addition, questionnaires about parental competencies, stress levels and services support will also be administered. The measures will be taken at trial time points outlined in Table 1.

**Table 1 Tab1:** TOBY Playpad Trial measures

Measure	Time points T0, T1, T2^a^ unless otherwise noted	Description
Primary Measure Autism Treatment Evaluation Checklist (ATEC) [64]		The ATEC is a parent rated measure consisting of four subtest scales: Scale I. Speech/Language/Communication (14 items—with scores ranging from 0 to 28); Scale II. Sociability (20 items— with scores ranging from 0 to 40); Scale III. Sensory/Cognitive Awareness (18 items— with scores ranging from 0 to 36), and Scale IV. Health/Physical Behaviour (25 items-with scores ranging from 0 to 75). The four subscale scores can be used to calculate a total score (with total scores ranging from 0 to 180). The higher the subscale and total score, the more impaired the participant. The lower the subscale and total score, the less impaired the participant.
Secondary Measures Autism Diagnostic Observation Schedule-Generic (ADOS-G) [58]	T0, T3	The ADOS-G is a semi-structured standardised observational assessment that uses questions and activities to elicit the communicative, social, and repetitive behaviours relevant to ASD diagnosis. There are four modules which are age and language dependent. Therefore, this trial will use Module 1 (for pre-verbal children or those using single words/simple phrases (10 activities with 29 accompanying ratings) and Module 2 (children with flexible phrase speech (14 activities with 28 accompanying ratings). A standardised severity score is generated for respective modules. The lower the severity score, the less impaired the participant.

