### Data collection

The trial data will be captured on a source document named the TOBY Participant Report Form (TPRF), primary and secondary measurement forms. The TPRF will be a de-identified document containing each participants unique study number, screening information, a log of informed consent obtained, results of direct baseline assessments, randomisation, all fortnightly follow up logs during the trial, protocol deviations and follow-up assessment results across T1 and T2. A TOBY trial databases will be developed and all data entry will occur at each site. This pragmatic trial may render minor protocol deviations in terms of timing of the follow-up assessments. Therefore, a window of two weeks will be considered as an acceptable time frame for attending all follow-up direct assessments whilst the return of self-reported completed questionnaires within two-to-four weeks of each time point will be acceptable.

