### Participant completion and withdrawal

Children in both arms of the study will be considered to have finished the trial upon completion of T2 direct assessments at 24 weeks post their baseline appointment. Those who do not to attend the 6 month follow-up direct assessments will be defined as withdrawn participants. This might reflect a parent or primary care giver’s decision to discontinue the TOBY intervention or to withdraw from the trial in general.

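### The stated analysis population includes every participant with outcome data, but one of the two named primary methods can drop a child who misses a single visit

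*Protocol article*

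**What the plan says.** In Sample size and analyses, the article sets the population: the analyses will be "performed on an intention-to-treat basis including all participants with outcomes data available". The next sentence sets the primary method: the ATEC total at three time points (taken here as T0, T1 and T2) "will be analysed using a repeated measures ANOVA or via a General Linear Model (GLM"). The article does not choose between the two methods, and does not say whether a child needs all three ATEC scores or only one.

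Three other places bear on which scores will exist:

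- Table 1: "The ATEC is a parent rated measure consisting of four subtest scales". It is not a direct assessment of the child.
- Data collection gives direct assessments a two-week window and treats questionnaires separately: "the return of self-reported completed questionnaires within two-to-four weeks of each time point will be acceptable".
- Participant completion and withdrawal: "Those who do not to attend the 6 month follow-up direct assessments will be defined as withdrawn participants".

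**The concern.** The population sentence keeps a child who has T0 and T2 but no T1, because that child has outcome data. A classical repeated measures ANOVA removes the same child. The two statements cannot both hold once any visit is missed. With the method left as a choice between two, the number and mix of children in the primary result could change with a decision taken after the data are seen.

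The withdrawal rule adds a smaller uncertainty. It turns on the clinic session at six months, while the primary outcome is a parent form with its own return window. A family can return a valid T2 ATEC and still be labelled withdrawn. If an analyst took that label as a reason to exclude, usable primary data would be lost.

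At stake are children and precision, and an intention-to-treat label that may not describe what is done.

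**Working it through.** **1. The plan's own figure.** Inputs from Sample size and analyses: effect size 0.2–0.5, power 80 %, two-sided alpha 0.05, about 64 per group, 10 % drop-out, 70 per group.

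n = 2(1.960 + 0.842)² / d². At d = 0.5 this is 2 × 7.85 / 0.25 = 62.8, so 63; the t-based version gives 63.8, so 64. For drop-out, 63 / 0.9 = 70 and 64 / 0.9 = 71.1. The stated 64 and 70 therefore reproduce within rounding, at the upper end of the effect range.

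**2. What the 10 % allowance covers.** 70 × 0.9 = 63 per arm; t-test power at d = 0.5 is 0.795. One loss of 10 % is covered.

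**3. What listwise deletion over two follow-ups would leave.** The article gives no missing rates by visit, so those below are assumptions. If losses are independent, complete cases = 70 × (1 − m1) × (1 − m2), where m1 and m2 are the proportions missing at T1 and T2. Power is for a two-sample t-test at one visit, d = 0.5.

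| Assumed loss | Complete per arm | Power |
|---|---|---|
| 10 % at T2 only, or the same 10 % at T1 and T2 | 63.0 | 0.795 |
| 5 % at T1, 10 % at T2, independent | 59.9 | 0.774 |
| 10 % at each, independent | 56.7 | 0.752 |
| 20 % at each, independent | 44.8 | 0.648 |

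To keep 64 complete children with an independent 10 % loss at each visit, 64 / 0.81 = 79.01 would be needed, so 80 per arm.

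**4. What a likelihood-based model would keep.** Under the same independent 10 % losses, the chance of missing both follow-ups is 0.1 × 0.1 = 0.01. On average 70 × 0.99 = 69.3 children per arm have at least one post-baseline ATEC, against 56.7 with all three scores.

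In one simulated data set of 140 children with this missingness, 121 had all three scores, 138 had at least one follow-up score and 140 had at least one ATEC. A mixed model accepted all 140. A classical repeated measures ANOVA routine rejected the incomplete data as unbalanced.

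**5. The withdrawal rule beside the population sentence.** The rule depends only on attending the T2 direct assessments. The population sentence depends only on having outcome data. A family that misses the clinic session but returns the T2 ATEC is withdrawn under the first and analysed under the second. No section says that withdrawn participants leave the analysis.

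**The case against.** The strongest reply is that the article does not commit to complete-case analysis. Its wording is available-case, and the GLM alternative could be fitted in a form that keeps incomplete children. That stands: a reader might infer that the intention-to-treat analysis is in fact complete-case, but the text supports this only for the repeated measures ANOVA option in classical form, and for a GLM procedure that also deletes incomplete rows. The restriction to participants with data is stated openly, and detailed missing-data rules may sit in a full protocol or SAP that is not shown. Their absence is not the point here. The point is that the article itself names a method that conflicts with its own population.

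A reader might also infer that withdrawn families are excluded, or that the rule confuses stopping TOBY with leaving the trial. Neither is supported. The rule defines completion status, and a family that stops TOBY but attends T2 is not withdrawn. Stopping TOBY is mentioned only as a possible reason for not attending, and App use is followed separately through the user account, calls and diaries.

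The power figures are fairly criticised too. They come from a single-visit t-test, whereas the plan uses three time points. If the T0–T2 correlation were 0.7 (an assumption), the SD of change is √(2 × 0.3) = 0.775 of the ATEC SD, the effect becomes 0.5 / 0.775 = 0.645, and 57 per arm give about 93 % power. At a correlation of 0.5 the figure is about 75 %.

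Finally, a reader might infer that deletion favours TOBY. Families know their allocation. After T2 the control arm is offered TOBY while the TOBY arm hands back the iPad, so reasons to attend may differ. The article gives no basis for the direction or size of any bias.

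**Conclusion.** The point holds in a limited form. The population sentence and one of the two named primary methods conflict as soon as a child misses one ATEC, and leaving the method open means the analysed set depends on the option chosen. The withdrawn label is not aligned with availability of the primary outcome, but on the text as written it removes nobody.

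The loss ranges from none beyond the plan (63 per arm, power about 0.80, if the same 10 % miss both follow-ups) to about 57 per arm (about 0.75) with an independent 10 % loss at each. These are illustrations under assumed missingness and a single-visit test. They do not show that 64 or 70 per group is wrong, and no bias figure is claimed. The correction is inexpensive and improves the primary analysis; the conflict does not by itself invalidate the trial.

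**What to change.** Before analysis starts, replace the choice of repeated measures ANOVA or GLM with one primary model: a likelihood-based linear mixed model for repeated measures, with unstructured covariance and baseline ATEC included. Analyse children in their allocated arm, using every returned ATEC from each randomised child with at least one post-baseline value. Name the T2 group difference as the primary contrast.

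Add one sentence to Participant completion and withdrawal: the withdrawn label refers to the T2 direct assessments and does not remove a returned parent-rated ATEC from the analysis.

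The cost is wording, standard software and slightly more modelling work. Trial status says data collection is complete and the data are being prepared for analysis, so no new data are needed and the choice can still be fixed in advance. The price is reliance on a missing-at-random assumption, which the plan should state.

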
The objectives of this study are:To determine the effectiveness of the TOBY Playpad App as a complement to early behavioural intervention as measured by a range of psychometric assessments which will assess core symptomology of ASD across time (baseline (Time 0), 3 months follow-up (Time 1) and 6 months follow-up (Time 2) through in-App data and parent reports.To determine whether the response to TOBY varies with variation of treatment intensity across both, TOBY + ‘therapy as usual’, and across different TOBY learning environments and syllabus.To measure the uptake of the TOBY intervention as recorded by the App and assessed by parents throughout the trial period using parent therapy diaries.To examine attitudes, perceptions and beliefs of parents towards TOBY as an intervention method as assessed by specific TOBY, family and parenting questionnaires over 6 months.To determine if TOBY intervention impacts on parental empowerment and stress levels.

We hypothesize that the TOBY App will improve children’s adaptive behaviours (language; social communication; restricted and repetitive behaviours) over time as assessed by a variety of measures at the final follow-up (6 months after starting the TOBY intervention). We also predict that parental empowerment in relation to the delivery of TOBY therapy will be enhanced at 6 months post randomisation. In addition, parental stress levels will be reduced as a result of the uptake of the TOBY intervention.

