### Study design

The TOBY Playpad study is a multisite, single (assessor) blind, randomised controlled pragmatic intervention trial with a parallel group design. Treatment in the form of early intervention delivered through an electronic platform like the iPad® using an application called the TOBY Playpad App in addition to ‘therapy as usual’ (TOBY therapy + therapy as usual) will constitute the treatment group. The ‘control’ group will receive any form of early intervention ‘therapy as usual’ accessed by the family through local service providers. Both groups will be assessed at baseline (Time 0) with two subsequent follow-ups at 3-(Time 1) and 6-months (Time 2) after the completion of baseline direct assessments including a battery of parent completed questionnaires. Figure 1 outlines the CONSORT flow diagram of this study.

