## Trial status

This is an ‘ongoing’ study. The data collection has been completed and it is being prepared for analyses.

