TOBY Playpad Intake Questionnaire	T0	The TOBY intake questionnaire consists of seven sections and is tailored to obtain parental report on children’s listening, communication, language and play skills. Items about children’s electronic media use and parents’ self-efficacy and confidence in assisting children to communicate are featured.
TOBY Playpad Follow-up & Satisfaction Questionnaire	T1, T2	The TOBY Playpad follow-up questionnaire version is as above. In addition, it contains 10 items and asks the treatment group parents (only) about the TOBY-App experience and satisfaction.
Case History Questionnaire (CHQ)	T0	The CHQ consists of eight sections and is tailored to gather socio-demographics of participants; birth; medical and developmental history of children with ASD. In addition, thinking styles of both biological parents in the form of Autism Quotient is asked.
TOBY therapy and therapy as usual Diary	T1, T2	Over 24 weeks of the intervention, both, intervention and control group parents report their children’s ‘therapy as usual’. In addition, the treatment group parents report TOBY App use termed as TOBY therapy. Both groups record relevant information at the end of each day in a diary format as featured in Fig. 3. Two diaries are provided to participants; 1) week 1–12 and 2) week 13–24.

^a^Data collection at T0 = baseline; T1 = follow-up 3 months; T2= follow-up 6 months

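### The primary ATEC model takes baseline as one of three repeated outcomes and ties no term to the six-month hypothesis; a baseline-adjusted six-month comparison would be a free improvement

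*Protocol article*

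**What the plan says.** The protocol article, under *Sample size and analyses*, states that the total ATEC score "at Time Points 1, 2 and 3 will be analysed using a repeated measures ANOVA or via a General Linear Model (GLM"). It does not say which term or contrast is the primary test, and it does not mention baseline ATEC as a covariate.

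*Study design* sets the schedule: "Both groups will be assessed at baseline (Time 0) with two subsequent follow-ups at 3-(Time 1) and 6-months (Time 2"). The footnote to Table 1 agrees: "T0 = baseline; T1 = follow-up 3 months; T2= follow-up 6 months". In *Background*, the main hypothesis is placed at the last visit, "as assessed by a variety of measures at the final follow-up (6 months after starting the TOBY intervention"). The same sentence also speaks of improvement as time passes, and the first objective spans all three assessments.

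The sample size rests on "a small-to-moderate effect size of 0.2–0.5" with 80% power and two-sided alpha 0.05. This gives about 64 per group, raised to 70 for 10% dropout. The ATEC SD is taken from "a difference of 1SD = 32 (30th-70th centile) on the ATEC".

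**The concern.** There are three assessments and three analysed occasions, so the numbering 1, 2, 3 can only stand for T0, T1 and T2. Table 1 does print a T3 label for the ADOS-G, but the footnote does not define it and no such visit is scheduled. Baseline is measured before treatment, so its expected group difference under randomisation is zero. Entering it as an outcome is harmless or harmful depending on the term then tested.

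A repeated measures model with group and time offers at least three candidate answers: the group main effect, the group-by-time interaction, and a contrast at 6 months. They have different targets and different power. The sample size is that of a single two-group comparison and is not linked to any of them. At stake are whether the primary result estimates the 6-month difference at all, and how much of the planned power survives.

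**Working it through.** **The plan's own figure.** For two means with d = 0.5, n = 2(1.960 + 0.842)² / 0.5² = 62.8, so 63 per group. The t-test version gives 63.8, so 64, which is the stated figure. For dropout, 63/0.9 = 70. The figure comes out only at the top of the stated range (d = 0.2 would need 393 per group). It describes one unadjusted comparison at one time point.

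**Inputs**
- From the article: 63 per group (70 less 10%), SD 32, d = 0.5 at 6 months (16 ATEC points), two-sided 5%.
- Assumed, because the article gives neither: equal correlation r between any two occasions, with r = 0.5 to 0.8; and a group difference at T0/T1/T2 of 0/0.25/0.5 SD (linear build-up) or 0/0.5/0.5 SD (full by 3 months).

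**Formulas** (unit SD; power from the noncentral t with noncentrality d·√(63/2), or from the noncentral F)
- Group main effect: mean difference over √((1+2r)/3). The mean difference is (0 + 0.25 + 0.5)/3 = 0.25 SD (8 points) in the linear case, and (0 + 0.5 + 0.5)/3 = 0.333 SD (10.7 points) if full by 3 months.
- Group-by-time: λ = (63/2)·Σ(δ_t − δ̄)²/(1−r), on 2 and 248 df. In the linear case Σ = 0.125, so λ = 3.94/(1−r). If full by 3 months, Σ = 0.167, so λ = 5.25/(1−r).
- T2 minus T0: d = 0.5/√(2(1−r)).
- T2 alone: d = 0.5.
- T2 adjusted for baseline: d = 0.5/√(1−r²).

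**Power (%)**

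| Term | r = 0.5 | 0.6 | 0.7 | 0.8 |
|---|---|---|---|---|
| Group main effect, linear | 40.0 | 36.9 | 34.4 | 32.1 |
| Group main effect, full by 3 months | 62.3 | 58.2 | 54.6 | 51.4 |
| Group-by-time, linear | 70.5 | 80.4 | 90.7 | 98.3 |
| Group-by-time, full by 3 months | 83.0 | 90.7 | 96.9 | 99.7 |
| T2 minus T0 | 79.5 | 87.6 | 94.9 | 99.3 |
| T2 alone | 79.5 | 79.5 | 79.5 | 79.5 |
| T2 adjusted for baseline | 89.5 | 93.6 | 97.4 | 99.6 |

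Worked example at r = 0.6, linear: the main effect has d = 0.25/√(2.2/3) = 0.292, giving 36.9%. The adjusted T2 comparison has d = 0.5/√(1−0.36) = 0.625, giving 93.6%.

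**Reading the table.** The main effect falls as correlation rises, because the average over occasions becomes less precise while the diluted effect stays the same. The interaction and the change contrast gain from correlation, because they use baseline through within-child change. The adjusted T2 comparison beats T2 alone and the change contrast throughout. It beats the interaction throughout in the linear case. If the effect is full by 3 months it beats the interaction up to r = 0.7, and at 0.8 the two are level.

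**The case against.** A reader might infer that the 6-month effect is diluted and the baseline score wasted. The article does not support that as a flat statement. Since it names no term, dilution follows only if the group main effect is read. In a parallel-group trial with a baseline visit, the group-by-time term is the natural reading. It uses baseline, is not averaged with it, and reaches 80% power from r = 0.6 upward even with linear build-up. This stands.

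A three-occasion analysis also fits the first objective and the hypothesis's mention of change as time passes. Baseline as an outcome is not an error in itself, since such a model can yield a valid 6-month contrast. Repeated measures ANOVA is itself a general linear model, and a GLM can carry a baseline covariate, so the either/or wording is less of a fork than it looks. These points stand too.

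A reader might further infer, from *Trial status* ("The data collection has been completed and it is being prepared for analyses"), that the model was still undecided after the last data were collected. That cannot be known: a condensed article leaves detail to a full protocol or SAP, and neither is shown.

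The objection does not remove two things. The sentence as printed puts baseline among the outcomes under labels that do not match the schedule, and the global interaction test, whatever its power, does not estimate the 6-month difference.

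**Conclusion.** The point holds in a conditional form. The stated model includes baseline ATEC as an outcome and links no term to the 6-month hypothesis. If the group main effect is read, power drops from the planned 80% to about 32–40% (linear build-up) or 51–62% (full by 3 months). A loss of half or more therefore depends on the assumed linear shape. If the interaction (71–98%, linear) or the change contrast (80–99%) is read, there is no dilution. The cost against a baseline-adjusted 6-month comparison (90–99.6%) is then one of efficiency, and it is small at high correlation.

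All ranges rest on 63 per group, a 0.5 SD effect at 6 months, equal correlations of 0.5–0.8 and complete data. The stated sample size is unaffected. This should be fixed because a better method is available at no cost. It does not show that the trial's primary analysis is invalid.

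**What to change.** Replace the analysis sentence with one model: a linear mixed model for ATEC total at T1 and T2, with T0 ATEC as a covariate and group, visit and group-by-visit terms. Make the group difference at T2, with its 95% CI, the sole primary test, and the T1 difference secondary. Relabel the occasions as T0 (covariate), T1 and T2. Do this before allocation is joined to the outcome data. If an unseen SAP already specifies such a contrast, the article need only be aligned with it.

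The cost is one paragraph of wording. Baseline ATEC is already collected, and no participants or visits are added.

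### The sample size is stated for an effect of 0.2–0.5 SD, but 64 per group gives 80% power only at 0.5 SD (16 ATEC points), half of the 32-point figure offered as clinically important and not linked to it

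*Protocol article*

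**What the plan says.** Everything relevant is in the Protocol article, section Sample size and analyses. The primary outcome is the ATEC total score (range 0–180, higher meaning more impaired). On the clinical judgment of two investigators, a score of 72 (the 50th centile) and "a difference of 1SD = 32 (30th-70th centile) on the ATEC can represent clinically important improvement in ASD symptoms".

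The next sentence sets the design target: "The aim of this intervention is to look for a small-to-moderate effect size of 0.2–0.5", with "80 % power and two-sided alpha of 0.05". The result follows: "This will require a sample of approximately 64 participants per treatment group". After a 10% allowance for drop-out, "70 participants will be required per treatment group, thus, the trial aims to recruit a total of up to 140 participants".

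No sentence connects the 32 points to the 0.2–0.5 target. The planned analysis is a repeated measures ANOVA or a general linear model.

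**The concern.** Two things do not fit together.

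- **The power statement.** One sample size is attached to a range of effects. A single n can have 80% power at only one effect size, so the statement can be true for at most one point in the range. A reader would take it that the trial can detect a small effect of 0.2 SD.
- **The clinical figure.** The number 32 serves as the SD and also as a difference said to be clinically important. The design effect is then set at no more than half of it, with no explanation. The 72 in the same sentence is a level on the scale. It cannot be an improvement unless a starting value is given.

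What is at stake is how the result is read. The trial sets out to determine effectiveness, and the Discussion foresees consequences for service provision and for parents' decisions. A significant difference of 11–16 points could be called effective on the strength of the power sentence, or short of clinical importance on the strength of the sentence before it. A null result could be taken as evidence against a small effect that the trial had little chance of detecting.

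**Working it through.** **Inputs, all from Sample size and analyses:** SD 32; effect size 0.2–0.5, taken as standardised by that SD; 80% power; two-sided alpha 0.05; 64 evaluable per group; equal allocation.

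**1. The range in ATEC points.** 0.2 × 32 = 6.4 and 0.5 × 32 = 16. Against 32 points these are 20% and 50%.

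**2. Reproducing the stated 64.** For two means, n per group = 2 × (1.960 + 0.842)² / d² = 15.70 / d².

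| d | Points | n per group, normal approximation | n per group, t-test | Power with 64 per group (t-test) |
|---|---|---|---|---|
| 0.2 | 6.4 | 393 | 394 | 20% |
| 0.5 | 16 | 63 | 64 | 80% |
| 1.0 | 32 | 16 | 17 | above 99.9% |

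The stated 64 is the d = 0.5 row. The 70 per group is consistent with 63 / 0.9 = 70 or 64 × 1.10 = 70.4.

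**3. Could adjustment rescue the 0.2 end?** If the analysis adjusts for baseline with correlation r, the required n is multiplied by (1 − r²). For 64 per group to give 80% power at d = 0.2, 1 − r² = 64 × 0.04 / 15.70 = 0.163, so r is about 0.91. The document gives no correlation, and 64 is what the unadjusted formula gives at 0.5.

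**4. Smallest significant difference.** Assume an unadjusted comparison at one time point. SE = 32 × √(2/64) = 5.66. With t(0.975, 126 df) = 1.979, the threshold is 1.979 × 5.66 = 11.2 points. That is 0.35 SD, or 35% of 32. With baseline adjustment the threshold is multiplied by √(1 − r²): 9.7 points at an assumed r = 0.5 and 8.0 at r = 0.7.

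**5. A result equal to the planned effect.** An observed difference of 16 has a 95% CI of 16 ± 11.2, that is 4.8 to 27.2, wholly below 32. If the true difference is 16, the chance of observing 32 or more is 1 − Φ(16 / 5.66) = 0.2%. This restates the gap between 16 and 32 and is not separate evidence.

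**6. Sensitivity to the SD.** If 32 is instead the 30th–70th centile span of a normal distribution, that span is 1.049 SD and the SD is 32 / 1.049 = 30.5. The target becomes 6.1–15.3 points and the picture does not change.

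**The case against.** The tempting stronger reading is that the protocol defines 32 points as its clinically important difference between groups and then sizes the trial for something else, so that the sample size is wrong or a positive result would contradict the protocol. The text does not support that reading, for these reasons.

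- The wording is soft. It says 32 points can represent important improvement. It does not call this a minimum, and it does not say whether it means change in one child or a difference between group means. The reference to clinical judgment in managing children fits a within-child reading at least as well. A worthwhile difference between group means can properly be smaller than an important change in one child.
- The 64 is derived from the effect size, not from 32, and it reproduces at 0.5 SD. Power for 32 points exceeds 99.9%. Planning for less than a benchmark is not an arithmetic error and does not make the trial too small.
- Rules for interpreting a significant result are commonly left to an analysis plan, which is not shown. Their absence from an article is not a fault.
- The 11-point threshold depends on an analysis simpler than the one planned.

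All four stand. They do not reach the power statement, which claims 80% for a range and delivers it only at the upper end. Nor do they supply the missing statement of what 32 means, which a reader needs in order to accept the within-child defence.

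**Conclusion.** The point holds as a misstatement of what the design delivers, together with an unreconciled clinical figure. With 64 per group the trial has 80% power at 0.5 SD (16 points) and about 20% at 0.2 SD (6.4 points), where about 393 per group would be needed. The powered effect is half of the 32 points, and the role of 32 is left open. On an unadjusted comparison at one time point, significance begins at about 11 points, roughly a third of 32. The practical gap is therefore 11–16 points against 32; an observed 6.4 points would not be significant in that comparison.

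The conclusion assumes that the effect size is standardised by the stated SD of 32 and that the power figure refers to an unadjusted two-group comparison, which is the calculation that returns 64. The significance threshold under the planned model depends on correlations that the document does not give. The consequence is for interpretation and reporting, not for the adequacy of the sample.

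**What to change.** Restate the design as SD 32, planned between-group difference 16 points (0.5 SD), 80% power, two-sided alpha 0.05, 64 evaluable per group. Drop the 0.2 end of the range, or keep it and state that its power is about 20%.

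Say what the 32 points refer to: the planning SD, a change within one child, or a between-group benchmark. Remove 72 as an improvement, since it is a level.

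Report the between-group difference at six months (T2) with its 95% CI, and set the 32-point figure beside it with its meaning stated, so that significance alone is not taken for clinical importance.

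Do not add a rule that bars any clinical claim when the CI excludes 32. With a true difference of 16, the upper limit falls below 32 whenever the observed difference is under 32 − 11.2 = 20.8 points. That happens with probability Φ(4.8 / 5.66), about 80%. Such a rule would usually block the claim at the planned effect, and it might apply a within-child figure to a group mean.

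The cost is wording only. Trial status says that data collection is complete, so the sample cannot change, but the data are still being prepared for analysis and the wording can be settled before the results are read. The downside is that the stated detectable effect becomes less favourable.

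### The 80% power stated for an effect size of 0.2–0.5 holds only at 0.5: with 64 per group, unadjusted power at 0.2 is about 20%

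*Protocol article*

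**What the plan says.** The sample-size reasoning is in the section Sample size and analyses of the protocol article. The primary outcome is the ATEC total score (range 0–180), to be analysed by repeated measures ANOVA or a general linear model over three time points. The section then states the target: "The aim of this intervention is to look for a small-to-moderate effect size of 0.2–0.5", "with 80 % power and two-sided alpha of 0.05". It continues: "This will require a sample of approximately 64 participants per treatment group". After the drop-out allowance, "70 participants will be required per treatment group, thus, the trial aims to recruit a total of up to 140 participants".

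The same section gives the scale and a clinical benchmark: "a difference of 1SD = 32 (30th-70th centile) on the ATEC can represent clinically important improvement in ASD symptoms".

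One sample size is thus attached to the whole range of effects. Nothing says that it applies only to the upper end, and no correlation between time points or baseline adjustment is given as an input to the calculation.

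**The concern.** When a power target is stated for a range of effects, the sample size has to satisfy it at the smallest effect in the range. Required sample size varies with the inverse square of the effect, so moving from 0.5 to 0.2 multiplies it by (0.5/0.2)² = 6.25. A single figure cannot give 80% power at both ends.

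What is at stake is how the result is read. The Trial status section says that data collection is complete and analysis is being prepared, so the power statement can now only frame interpretation. A reader who believes that the trial had 80% power down to 0.2 SD would take a null ATEC result as good evidence against a small effect, and the design does not support that.

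**Working it through.** **Inputs, all from Sample size and analyses.** Standardised effect d from 0.2 to 0.5; power 80%; two-sided alpha 0.05; 64 evaluable per group, equal groups; SD of the ATEC total 32 points, so 0.2 SD = 6.4 points and 0.5 SD = 16 points.

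**Step 1: reproduce the plan's figure.** For two means, n per group = 2(1.960 + 0.842)²/d² = 15.70/d². At d = 0.5 this is 15.70/0.25 = 62.8, so 63. The exact t-test gives 63.8, so 64, which is the stated figure.

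**Step 2: apply the same calculation to the rest of the range.** At d = 0.2, 15.70/0.04 = 392.5, so 393; the t-test gives 394. That is 394/64, or about 6.2 times the stated number. Power with 64 per group is approximately Φ(d√(64/2) − 1.960). At d = 0.2 this is Φ(1.131 − 1.960) = Φ(−0.829) = 20.4%. The t-test figures are:

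| d | ATEC points at SD 32 | n per group for 80% power | Power with 64 per group |
|---|---|---|---|
| 0.2 | 6.4 | 394 | 20% |
| 0.3 | 9.6 | 176 | 39% |
| 0.4 | 12.8 | 100 | 61% |
| 0.5 | 16.0 | 64 | 80% |

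**Step 3: try other readings of the sentence at its lower end.** A one-sided test at d = 0.2 needs 310 per group and has 30% power with 64. If 0.2 were Cohen's f, then d = 0.4, which needs 100 per group and has 61% power with 64. Neither reaches 80%.

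**Step 4: allow for the planned analysis.** The protocol gives no correlation, so I assume 0.5 to 0.8 between time points, with compound symmetry. The variance is multiplied by:

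- 1 − r² for one follow-up adjusted for baseline: 0.75 to 0.36. Power at 0.2 with 64 per group is 26% to 47%.
- (1 + r)/2 − r² for the mean of two follow-ups adjusted for baseline: 0.50 to 0.26. Power is 36% to 60%.
- 2(1 − r) for change scores: 1.0 to 0.4. Power is 20% to 43%.

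For 64 per group to give 80% power at 0.2, the factor would have to be 64 × 0.04/15.70 = 0.163, which implies a correlation of about 0.9. With that factor, n at d = 0.5 would be 62.8 × 0.163, or about 10 per group. So 64 was not obtained in that way.

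**Step 5: what a null result could exclude.** The unadjusted 95% confidence interval has half-width 1.98 × √(2/64) = 0.35 SD, or about 11 ATEC points (0.35 × 32 = 11.2).

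**The case against.** The strongest objection is that the t-test is not the planned analysis. A repeated-measures or baseline-adjusted model usually has more power. Under the correlations assumed above, the effect detectable with 80% power and 64 per group falls from 0.50 to 0.43–0.30 (one follow-up) or 0.35–0.25 (mean of two). This stands to the extent that the 20%, 39% and 61% must be labelled as unadjusted figures. It does not rescue the claim at 0.2, where power stays at 60% or less over that range.

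A reader might go further and infer that the trial cannot detect anything clearly below 0.5 SD, or that a null result could not rule out most of the target range. The documents do not support either. Unadjusted power at 0.4 is 61%, and an observed difference of about 0.35 SD would reach significance. A null estimate near zero would exclude roughly 0.35 to 0.5 and leave roughly 0.2 to 0.35 open.

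A reader might also count the drop-out allowance as an error, since 70 × 0.9 = 63 falls short of 64. The protocol says approximately 64, and 63 per group still gives 79.5% power at 0.5 against 80.1% with 64. That is not material.

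Finally, the section calls 32 points clinically important, and power for 32 points (d = 1) with 64 per group exceeds 99%. This is fair, and it means that 16 points should not simply be adopted as the yardstick. It does not make the 0.2–0.5 statement correct.

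**Conclusion.** The power statement is wrong as written. About 64 per group gives 80% power at 0.5 SD, the top of the stated range, and about 20% at the bottom of it under the calculation that produces 64. These figures rest on an unadjusted two-sample t-test with equal groups and two-sided alpha 0.05. Baseline adjustment could raise power at 0.2 to about 25% to 60%, but that depends on assumed correlations of 0.5 to 0.8 that the protocol does not give. An analysis plan that is not shown could set out the model, but it could not make this numerical statement true.

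The error affects how a null result is interpreted. It does not affect the type I error, the primary outcome or the estimate itself.

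**What to change.** Replace the 0.2–0.5 power claim with wording to this effect: *about 64 evaluable children per group give 80% power for a standardised difference of 0.5 (16 ATEC points at SD 32) in an unadjusted two-group comparison; power for smaller effects is lower (about 20% at 0.2, 39% at 0.3 and 61% at 0.4).*

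Add one sentence that relates the 0.5 SD target to the 32-point difference that the same section calls clinically important, since the two now stand side by side without explanation.

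Report the ATEC difference with its 95% confidence interval, so that a null result is not read as excluding small effects.

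The cost is wording only. No extra recruitment is proposed and the analysis is unchanged, though the stated target becomes less favourable.
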